**Methods:**

This is a prospective, randomized, multicenter clinical trial. One thousand one hundred forty primary and secondary school students aged 8–18 years old from 27 schools will be recruited and randomly divided into an experimental and a control group at a ratio of 2:1 in two phases, with a training period of 30 days in each phase and a follow-up period of 3 months. No interventions will be conducted during the follow-up period, nor will other interventions employed. Inclusion criteria will meet the diagnostic criteria for simple myopia and −6.00D ≤ spherical lenses ≤ −0.50D and cylindrical lenses ≤1.50D. The primary observation index will be to compare the statistical differences in distant visual acuity between the two groups; the secondary observation indexes will be ocular symptoms (mainly including eye fatigue, dryness, pain, double vision, neck pain, thought disorders, and lags in response), diopter, and astigmatism.

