Currently, optical correction by glasses is the main intervention method for simple myopia, but it cannot improve the visual acuity of the naked eye. Drugs such as atropine can improve visual acuity, but once the drug is discontinued, the vision problem will rebound or cause even worsen myopia, along with some side effects such as photophobia, blurred vision, and allergic conjunctivitis [7]. Laser surgery may be complicated by other eye diseases, such as near vision impairment and dry eye, and has age restrictions [8, 9].

Vision acuity training refers to the use of optical, psychological, physical, and other methods to produce a certain cognitive load on the visual system of the eyes (including regulation, convergence, eye movements, and the associated movements between them), in a bid to improve the visual function and visual comfort of the visual system and achieve the goal of improving and repairing visual abnormalities in both eyes. It is considered as a purely physical, non-invasive, non-drug therapy with no side effects to relieve eye fatigue and improve vision, with a long history. The earliest and most widely known is the Bates Vision Acuity Training Method, including eye sunbathing, palm massage, rope games, ruler games, pencil games, etc. But due to the complexity of its training, long cycles, etc., it has not been widely promoted. At present, the common vision training mainly relieves the ciliary muscle tension by repeatedly focusing on the distant visual target, looking at the distance and movement of the image to adjust the function of the extraocular muscles, and through the different light color changes to stimulate the visual cortex, as ways to improve vision and restore to a good visual system.

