***Enrollment***																
Screening visit		×														
Informed consent		×														
Inclusion and exclusion criteria		×														
History of myopia Intervention		×														
Diet habits		×	×													
Daily activity time distribution		×	×													
CISS^†^		×	×					×	×	×					×	×
Diagnosis		×						×	×	×						
Randomization			×													
Subject files		×						×	×	×						
Adverse events				×	×	×	×	×	×	×	×	×	×	×	×	×
Quit in advance				×	×	×	×				×	×	×	×	×	
Unscheduled visits								×	×	×						×
Allocation			×													

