### Exclusion criteria

Those who have comorbidities or complications of other eye diseases, such as glaucoma, amblyopia, eye infections, etc.Those who have comorbidities of very severe heart, brain, liver, kidneys, hematopoietic system diseases and neuropsychiatric diseases, or systemic diseases that may affect the progression of myopiaThose who have had eye surgery or a history of eye traumaThose who have comorbidities of hearing abnormalitiesThose who are unable to cooperate with the study for personal or family reasonsThose who refuse to sign an informed consent form by himself/herself or any of his/her guardians

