### Excluded cases

Those who with any of the following should be excluded:
Subjects with incomplete case information that affects the analysis of the trial results. For subjects, who missed 4 or more days in the first 7 days of treatment, or participated in daily training for less than 14 days. Patients with lost contact were followed up without corresponding prediction and correlation analysis. For research, more than half of the cases in which data was lost due to machine failure or forgetting to record.Subjects with poor compliance during the trial due to subjective or objective factors of their own or family members. Who shows obvious resistance, fall asleep, or play during training and continue to do so after being reminded by the researchers.Subjects who use other interventions for myopia outside the protocol: drug therapy, acupuncture, orthokeratology, etc.

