### Primary observation indexes

Visual acuity training aims to improve naked eye visual acuity, which affects life and work and will be used as the main observation index. Visual acuity tests were performed before and after each training session for the first 7 days, once a week after 7 days of training and at the first, second, and third months of follow-up, respectively.

The specification for visual acuity testing is based on the “Expert Consensus on Workflow of Myopia Screening in Children and Adolescents (2019)” [21]. The international standard logarithmic visual acuity chart is adopted. During the measurement, the subjects stand 5 m away from the visual acuity chart and cover the contralateral eyes without squinting and oppression. The covered eyes are examined first in the right eye and then in the left eye. If the inspector can identify half or more of the visual markers, check them line by line from top to bottom and ask the subjects to say or gesture the direction of the gap of the visual markers within 5 s. The last line of the visual markers that is correct will be the testee’s vision of that eye. For example, if row 4.8 cannot be identified, check upward until half or more of the rows can be identified.

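### Current or recent myopia treatment does not bar entry, although the same treatments exclude a child after randomisation

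*Protocol article*

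**What the plan says.** - **Entry.** The Inclusion criteria ask for age 8 to 18, simple myopia within refractive limits, normal corrected vision, ability to cooperate, and consent. The Exclusion criteria start with "Those who have comorbidities or complications of other eye diseases, such as glaucoma, amblyopia, eye infections, etc" and go on to severe systemic or neuropsychiatric disease, eye surgery or trauma, hearing problems, non-cooperation and refusal of consent. Drugs, acupuncture and orthokeratology appear in neither list.
- **Recorded at enrolment.** Table 1 schedules "History of myopia Intervention" at the enrolment visit. No eligibility rule refers to it, and Randomization names region, age and gender as strata but not prior treatment.
- **After randomisation.** Excluded cases removes "Subjects who use other interventions for myopia outside the protocol: drug therapy, acupuncture, orthokeratology, etc". The same section covers children who "missed 4 or more days in the first 7 days of treatment", so it acts once training is under way.
- **During the trial.** The Abstract says "No interventions will be conducted during the follow-up period, nor will other interventions employed". Intervention description makes a similar statement for both the treatment and follow-up periods, evidently meaning nothing outside the protocol.
- **Stopping a drug.** Of drugs such as atropine, the Background says "once the drug is discontinued, the vision problem will rebound or cause even worsen myopia".
- **Outcome.** "Visual acuity training aims to improve naked eye visual acuity, which affects life and work and will be used as the main observation index". Diopter and astigmatism are secondary.

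**The concern.** The sponsor regards these treatments as incompatible with the trial and collects the relevant history before allocation, yet acts on it only afterwards. An ineligibility that could be settled at screening becomes an exclusion made when child, family and trial staff know the arm.

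The alternative, stopping treatment to comply, is not neutral on the protocol's own account. For drugs such as atropine it describes rebound or worsening on discontinuation, in a trial whose primary outcome is unaided acuity. At stake are avoidable exclusions, extra variation in acuity and refraction, and a possible distortion of the phase 2 comparison.

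**Working it through.** No figure in the plan bears directly on this point, so the check is mainly of the text.

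**Step 1. The rules side by side.**

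| Section | When it acts | Names drugs, acupuncture or orthokeratology? |
|---|---|---|
| Recruitment, Inclusion criteria | Before randomisation | No |
| Exclusion criteria | Before randomisation | No; eye surgery is the only treatment named |
| Table 1, enrolment | Before randomisation | History recorded, no rule attached |
| Randomization (strata) | At allocation | No |
| Excluded cases | After training starts | Yes, as grounds for exclusion |

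**Step 2. Follow a treated child through.** Take a child on one of the listed treatments who meets the diagnostic reference in Recruitment and the Inclusion criteria. Nothing stops randomisation. Two paths follow.

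1. Treatment continues. Read literally, the child meets the Excluded cases rule from the first training day.
2. Treatment stops. For a drug such as atropine, the Background predicts rebound or worsening. It gives no timing, so part or all of the change could fall within the 30-day training and 3-month follow-up.

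**Step 3. Where bias could arise.**

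- *Phase 1, between arms.* Treatment at entry precedes allocation and is balanced in expectation. Equal rebound in both arms adds noise, not bias. Bias needs continuing, stopping, resuming or being removed to differ by arm. That is possible because Implementation leaves subjects and those running the trial unblinded.
- *Phase 2.* Second phase compares the phase 1 controls' results under meditation training with their own earlier results under eye exercises, and the Discussion calls this a single-arm pre-post design. A rebound concentrated in phase 1 would depress the eye-exercise results and flatter the later training. Randomisation cannot balance that.

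**Step 4. Size.** The documents give no share of treated children, so a range is assumed. Inputs from Sample size: means 4.98 and 4.92 (difference 0.06), SDs 0.14 (experimental) and 0.24 (control), 760 and 380 children, 20% dropout, two-sided 0.05.

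Power = Φ(0.06 / √(0.24²/n_C + 0.14²/n_E) − 1.96)

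After dropout, n_E = 760 × 0.8 = 608 and n_C = 380 × 0.8 = 304. The standard error is √(0.0576/304 + 0.0196/608) = 0.0149, and 0.06/0.0149 − 1.96 = 2.07, so power is 0.981. Removing a further fraction f multiplies both group sizes by (1 − f):

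| Assumed share f | Removed of 1140 | Kept, before dropout | Power, after 20% dropout |
|---|---|---|---|
| 5% | 57 | 1083 | 0.975 |
| 10% | 114 | 1026 | 0.969 |
| 20% | 228 | 912 | 0.950 |
| 30% | 342 | 798 | 0.921 |

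These are individual-level figures with no allowance for clustering by school. Even at 30%, power stays above the planned 0.90.

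**The case against.** **The entry rules screen out some treated children.** Recruitment requires distance acuity below 1.0, normal near acuity and slow progression. An orthokeratology user whose unaided acuity is 1.0 or better fails, and a child already worsening at screening arguably does too. This stands, but the screen is partial: a child who stops treatment at enrolment, or whose acuity is still below 1.0 on treatment, can pass.

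**Excluded cases may mean only treatment taken up during the trial, or may only define the Per Protocol Set.** Statistical analysis plans both a Full Analysis Set and a Per Protocol Set, and Missing data evaluates all randomised patients whatever their adherence. Both readings are possible, so it is not settled that these children leave every analysis. Neither reading keeps them out of the trial: if they stay in, outside treatment or its withdrawal enters the acuity data.

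**Broad entry can be a deliberate choice in a school-based trial.** It can, but it sits badly with a later rule that excludes for the same treatments.

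**Stronger readings that a reader might infer, and that the documents do not support:**

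- *That treated or rebounding children will be randomised in known numbers.* The text shows only that they can be.
- *That stopping any listed treatment causes rebound within the trial.* The Background says this only of drugs such as atropine, and gives no timing.
- *That the gap by itself shifts the phase 1 difference by some stated amount.* That needs an assumed imbalance between arms and an assumed size of rebound. The documents give neither, and randomisation would not be expected to produce the imbalance.
- *That spectacle wearers could be removed, because the Background says "optical correction by glasses is the main intervention method for simple myopia" and the list is open-ended.* This is strained. The Background adds that glasses do not improve unaided acuity, and the Inclusion criteria require normal corrected vision.

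**Conclusion.** The point holds as a gap between stated rules. Children currently or recently on drug therapy, acupuncture or orthokeratology who meet the remaining criteria can be randomised and can then meet an exclusion for those treatments, although their history is recorded beforehand. The article sets out its entry criteria as full lists and names the treatments elsewhere, so condensation for publication does not explain the mismatch.

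The size is unknown because the share of treated children is not given; 57 to 114 children corresponds to an assumed 5% to 10%. Loss of power is minor. The main consequences are avoidable exclusions after an unblinded allocation, added noise in acuity and refraction in phase 1, and possible bias in the phase 2 versus phase 1 comparison if rebound falls mostly in phase 1. Bias between arms in phase 1 is conditional on behaviour or removal differing by arm. This should be corrected, but it does not by itself undermine the randomised comparison.

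**What to change.** Reconcile Table 1, Inclusion criteria, Exclusion criteria and Excluded cases:

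1. Apply the sponsor's own treatment list from Excluded cases as an exclusion before randomisation, using the history already collected at enrolment.
2. Have the sponsor state how recently stopped treatment is handled at entry. Any time limit is for its ophthalmology team to set.
3. Limit the Excluded cases rule to treatment started after randomisation.

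The cost is protocol wording. No new data item is needed. Some screened children would become ineligible, which would slow recruitment slightly.

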## Randomization

The random sequence will be designed and processed by the research team of Beijing University of Chinese Medicine. SPSS 20.0 (SPSS Inc., Chicago, IL, USA) software will be used to generate serial numbers for the subjects. Multiple factors that affect this trial will be taken into consideration. Participants from different areas with similar school level will be stratified. A stratified randomizing method will also be adopted according to region, age, gender, etc. Similar stratified groups will be compared; the experimental and the control groups are launched within the same school.

As this study will cover 27 schools, a multicenter trial, stratified randomization will be adopted. Firstly, 27 schools will be allotted east, west, north, south, and middle regions of China. Secondly, schools in each district will be divided into 3 layers according to age. Children aged 8–11 years, 12–14 years, and 15–18 years, severally. This method will minimize errors and improve accuracy.

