### Recruitment

In this trial, 1140 primary and secondary school students with simple myopia will be recruited from 27 schools in Sichuan and Hunan provinces or other cities with relatively uniform schooling conditions. School factors will be taken into consideration. We will choose participates from different areas with similar teaching level as the subjects. In the meanwhile, a comparison of the experimental group and the control group is launched within the same school in order to reduce the variance.

The main points for the diagnosis of simple myopia in China’s “Myopia Prevention and Treatment Guidelines” [19] will be used as a reference standard for recruitment: near visual acuity is normal; distance visual acuity is less than 1.0 (5.0 by the mucosal method); there are no pathological changes in the fundus; the progression is slow; vision can be corrected to normal with appropriate lenses, while other visual function indicators are mostly normal; and the subject recruited meet the quantitative criteria for myopia according to the “White Paper on Myopia Prevention and Control” of the International Myopia Institute (IMI) [20]: myopia diopter ≤ −0.50D.

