## Statistical analysis

### Sample size

The sample size will be estimated based on our early observations [23]. The treatment group was 4.98 ± 0.14, and the control group was 4.92 ± 0.24. Under 20% dropout rate, with the two-tailed *α* = 0.05 and *β* = 0.1 (test efficacy of 0.9), experimental group: control group = 2:1, PASS 15.0 software calculation shows 380 in the experimental group and 190 in the control group. Due to the possible center effect, the final sample size is suggested to be twice expanded. Thus, it is finally confirmed there will be 1140 cases in total, with 760 cases in the experimental group and 380 cases in the control group.

Statisticians suggest that we appropriately expand the sample size to reduce the impact of the central effect on the final results.

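### Randomisation is stratified by region and age layer without naming school, although the arms are to be compared within school; the cost is a modest loss of precision, not bias

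*Protocol article*

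**What the plan says.** The Randomization section of the protocol article names its factors: "A stratified randomizing method will also be adopted according to region, age, gender, etc". It then gives a two-step scheme. First, "27 schools will be allotted east, west, north, south, and middle regions of China". Second, "schools in each district will be divided into 3 layers according to age", the layers being 8–11, 12–14 and 15–18 years. School does not appear as a stratum.

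The same section says that "the experimental and the control groups are launched within the same school", and the Statistical analysis section repeats this. The Recruitment section gives the purpose: "a comparison of the experimental group and the control group is launched within the same school in order to reduce the variance".

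The Sample size section treats between-school variation as a real threat: "Due to the possible center effect, the final sample size is suggested to be twice expanded". This takes 380 + 190 to 760 + 380.

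The Statistical analysis section proposes a linear mixed model and justifies it by the repeated acuity measurements. It names no school effect there, and it states that acuity values of different subjects are independent.

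**The concern.** School is both the source of variation that the sample size section fears and the unit within which the arms are to be compared. The stated strata are coarser. Region is determined by school, so it adds nothing once school is a stratum. A list shared by several schools in one region or region-by-age cell holds 2:1 over the cell but not in each school.

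Chance differences in the arm mix between schools then carry between-school variation into an unadjusted treatment contrast. Doubling the total dilutes that component. Balancing and adjusting by school removes it. Independence between children also conflicts with a centre effect: if schools differ, children in the same school are correlated.

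What is at stake is precision. Children are randomised individually, so the contrast is valid with or without school strata.

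**Working it through.** **Inputs from the protocol article.** 27 schools; 1140 children, 2:1 (760/380); five regions; three age layers; "The treatment group was 4.98 ± 0.14, and the control group was 4.92 ± 0.24"; two-sided alpha 0.05; power 0.90; dropout 20%.

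**The plan's own figure.** The doubling is exact: 2 × 380 = 760, 2 × 190 = 380, total 1140. The base of 380/190 does not reproduce from the stated inputs. The unequal-SD formula n_control = (0.14²/2 + 0.24²)(1.96 + 1.28)²/0.06² gives 197 control and 394 experimental, or 247 and 493 after dividing by 0.8. That is a separate matter and does not affect this point.

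**School size.** 1140/27 = 42.2, so take m = 42, about 28 experimental and 14 control.

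**Assumptions, none from the article.** Schools are equal in size; each cell is balanced at exactly 2:1; region and age explain none of the between-school variance; gender is ignored; the intraclass correlation ρ is 0.05, 0.10 or 0.20; a single acuity value is compared.

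**Variance inflation without school in the analysis.** Scale the total variance to 1. In a cell of c schools, the variance of the treatment difference is proportional to the expected within-cell variance:

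(1 − ρ) + ρ·m(c − 1)/(cm − 1).

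With school as the stratum, c = 1 and this is 1 − ρ. The ratio is therefore 1 + f·ρ/(1 − ρ), where f is the average of m(c − 1)/(cm − 1) over schools.

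- *Five regions only*, with 6, 6, 5, 5 and 5 schools: 210/251 = 0.837 for c = 6 and 168/209 = 0.804 for c = 5, so f = (12 × 0.837 + 15 × 0.804)/27 = 0.818.
- *15 region-by-age cells*, each school in one age layer, 12 cells of two schools and 3 of one: 42/83 = 0.506 for c = 2 and 0 for c = 1, so f = 24 × 0.506/27 = 0.450.

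| Assumed ρ | ρ/(1 − ρ) | Five regions | 15 cells |
|---|---|---|---|
| 0.05 | 0.053 | 1.04 | 1.02 |
| 0.10 | 0.111 | 1.09 | 1.05 |
| 0.20 | 0.250 | 1.20 | 1.11 |

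If schools span several age layers, a cell holds parts of more schools and the result moves towards the five-region column.

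**Loss that remains with school in the model.** Information within a school is proportional to p(1 − p), where p is its experimental share. Its expectation falls by the fraction f/m from the balanced value 2/9. The variance ratio is 1/(1 − f/m):

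- five regions: 1/(1 − 0.818/42) = 1.02;
- 15 cells: 1/(1 − 0.450/42) = 1.01.

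**Effect on power.** After 20% dropout the doubled sample is 608/304. The standard error is √(0.14²/608 + 0.24²/304) = 0.0149, and 0.06/0.0149 = 4.03. Power is Φ(4.03 − 1.96) = 0.98. With the largest inflation in the table, 1.20, it is Φ(4.03/√1.20 − 1.96) = 0.96. This is cautious, because the quoted SDs may already include between-school variation.

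**The case against.** **The text may already intend allocation within school.** The article says school factors will be considered, the factor list is open-ended, and the Quality control section gives each arm its own classroom and teachers. This supports both arms being present in each school. It does not make school a stratum, and the two-step scheme that follows describes something else. If lists per school were meant, the text should say so.

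**A school term belongs in the statistical analysis plan.** This stands in part. The absence of a school effect from the article would not be a finding by itself. The article does, however, state independence between children, and that conflicts with its own reason for doubling the sample.

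**The practical consequence is small.** This stands. There is no bias, power on the stated inputs stays above 0.95, and a school term alone recovers nearly all of the loss.

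**Stronger readings that the article does not support.** A reader might infer that the precision of the within-school design is lost, or that some schools would lack an arm. With about 42 children per school at 2:1, both arms would normally be present. A reader might also compute the loss as if allocation were unrestricted: f = 0.964, giving 5%, 11% and 24%. The article specifies stratified allocation, so those figures are upper bounds. A cluster-trial design effect does not apply either, because schools are not the unit of allocation. Lastly, the Recruitment section names two provinces but allows other cities, so it cannot be said that five regions will go unfilled.

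**Conclusion.** The point holds as a correctable mismatch between the aim and the stated method. The arms are to be compared within school and a centre effect is expected, but the strata stop at region and age layer, and the analysis text assumes independence between children.

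Without school in the analysis, the variance is about 4–20% larger if only regions are balanced and about 2–11% larger with 15 cells, over assumed intraclass correlations of 0.05 to 0.20. With school in the model the loss is about 1–2%. These sizes rest on equal schools of 42, exact balance per cell and an assumed spread of schools over cells. They would be smaller for an analysis adjusted for region and age if those factors explain part of the school differences. The change is worth making because it costs little and matches the stated aim; the validity of the trial does not depend on it.

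**What to change.** 1. In the Randomization section, name school as the stratum in place of region: blocked 2:1 lists per school, split by age layer only where a school spans more than one. Apply this to schools that have not started.
2. In the Statistical analysis section, include school and age layer as terms in the linear mixed model, for all schools. This brings nearly all of the gain even where the lists cannot be changed.
3. Remove or correct the statement that acuity is independent between subjects, so that it agrees with the expected centre effect.

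No extra children or visits are needed. The cost is regenerating the lists and short edits to two sections. The Trial status section reports recruitment as ongoing and first enrolment in December 2021, so some schools may already have begun; the date of the change should then be recorded. School as a fixed effect uses 26 degrees of freedom, which is minor with 1140 children.
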